1. ***Blinding. [Blinding is used in treatment studies and diagnostic trials to reduce the risk of implementation bias and measurement bias. Implementing strict confidentiality measures, such as using placebos or simulating procedures, is an effective blinding method. If blinding is necessary and feasible for your study, describe the methods and procedures for implementing blinding]***

This trial includes group therapy sessions for students from the same school. As a result, participants may already know each other or be unfamiliar with one another, and they may naturally discuss the experimental training they receive. Maintaining blinding for the researchers is challenging as they may be influenced by the experimental content during the trial. Therefore, meeting the requirements of double-blinding in a clinical trial is not feasible in this situation

1. ***Outcome Measures. [Outcome measures are used to evaluate the results of a study and can include primary, secondary, and safety measures, including adverse events and reactions. Please describe the names of the measures, the methods of measurement, and the time points at which they are assessed]***

As listed in **Table 1**, the primary outcomes include subjective reports of smoking craving, changes in EEG indicators, and mindfulness measures (both trait- and state- mindfulness). The secondary outcomes will be daily smoking behaviours (number of cigarettes smoked per day, exhaled carbon monoxide concentration), affect and impulsivity, as well as indicators reflecting correlation between mindfulness and smoking cue-reactivity. Researchers will inquire daily during the intervention period whether participants experience tobacco withdrawal symptoms or any other adverse reactions. Participants are also encouraged to proactively contact the research team if they experience any adverse reactions. Please refer to item 9 for the time points of assessment.

| **Table 1. Evaluated variables** | | | |
| --- | --- | --- | --- |
| **Variables** | **Timepoints** | **Measures** | **Outcome level** |
| **Category 1: smoking related indices** | | | |
| **Nicotine dependence** | -T1, T0, T1-T5 | **Fagerstrőm test for nicotine dependence (FTND)** is a six-item revision of the Fagerstrőm Tolerance Questionnaire **^[31]^**，scored as 0-3 (low), 4-6 (moderate), and 7-10 (high) with the summed score **^[32]^**. | primary |

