| **Anxiety** | -T1 | **Generalized Anxiety Disorder (GAD-7)** used to measure anxiety related problems over the past two weeks, with each project scoring 0-3 points and a total score of 0-21 points **^[25]^**, with scores of 5, 10, and 15 corresponding to the cutoff values for "mild", "moderate", and "severe" anxiety levels **^[45]^**. | others |

*CR: cue-reactivity.

1. ***Definition of Participant Effectiveness Determination. [This includes definitions for participant withdrawal, exclusion, loss to follow-up, confounding factors, study discontinuation, and study suspension]***

(1) **Participant Withdrawal:** Each participant has the right to withdraw from the study at any time without the need to provide a reason. Participants who choose to withdraw voluntarily will not be included in the analysis. As part of our comprehensive research procedure, we have established a protocol for managing participants who decide to withdraw. If participants are willing to provide a reason for their withdrawal, it will be documented and recorded.

(2) **Participant Exclusion:** Due to the inability to ensure full intervention participation in the intervention group during the training process, the "STOP" training period lasts for one week. Participants who have participated in less than 5 training sessions will be considered as not having received the complete intervention and, theoretically, should be excluded or adjusted using mixed effects models.

(3) **Participant Loss to Follow-up:** If a participant cannot be contacted for two consecutive visits after the completion of the intervention for any reason, they will be classified as lost to follow-up.

(4) **Participant Contamination:** Following the completion of the intervention, a survey will be conducted with the participants. If the control group attempts to learn about the training mode used by the intervention group (or vice versa) and attempts to replicate the training, they will be classified as contaminated participants.

(5) **Participant Termination:** To prioritize participant health, any adverse events (including tobacco withdrawal symptoms) will be considered termination criteria. Researchers will discuss with the participant who experiencing such conditions and terminate the intervention early. Participants will receive appropriate clinical interventions only with their explicit consent.

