(6) **Participant Suspension:** Participants in this study can request to suspend the intervention. If a suspension is requested, the participant will be evaluated by the study team and, if approved, moved to the future intervention group. Data collected before the suspension will not be included in the final data analysis.

1. ***Definition, identification methods, and management systems for adverse events and reactions.***

In the "Chinese Clinical Smoking Cessation Guidelines," it is stated that smokers may experience a range of withdrawal symptoms after quitting or reducing smoking. These symptoms include smoking cravings, anxiety, depression, restlessness, headache, increased salivary gland secretion, lack of concentration, and sleep disorders. Withdrawal symptoms typically begin within hours of smoking cessation, peak within the first 14 days, and gradually diminish until they disappear. Most withdrawal symptoms last for about one month, although some patients may experience cravings for smoking for over a year.

**Definition:** Adverse events refer to any unfavorable or unintended signs, symptoms, or diseases that occur during or after the intervention, regardless of whether they are related to the intervention. Adverse reactions specifically refer to unfavorable or unintended responses that are causally related to the intervention.

**Identification Methods:** Adverse events and adverse reactions can be identified through various methods, including participant self-reporting, researcher observations, physical examinations, laboratory tests, and medical records.

**Management System:** In light of the potential adverse reactions mentioned above, the researchers will conduct daily inquiries during the intervention to determine whether participants have experienced any of the symptom. The delivered list will also provide information to participants, instructing them to promptly contact the researchers if they experience similar symptoms at any other time. In the event of any adverse reactions, responsible personnel from the medical school and psychology department will promptly contact the participants and assess their psychological and physiological conditions. Based on the participant's willingness, a collective decision will be made by the medical school, psychology department, and participant regarding their continued participation in the subsequent research. The researchers will record the reasons for their decision.

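### The rule for ending training after an adverse event has no severity threshold, covers expected withdrawal symptoms including craving, and is not linked to the joint-decision rule for the same symptoms

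*Protocol*

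**What the plan says.** Two sections of the protocol govern what happens when a participant reports a symptom.

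- **Definition of Participant Effectiveness Determination, item (5), Participant Termination.** On grounds of participant health, "any adverse events (including tobacco withdrawal symptoms) will be considered termination criteria". The action follows: "Researchers will discuss with the participant who experiencing such conditions and terminate the intervention early". No grade, duration or causal link is required, and termination is the only result stated.
- **The section on adverse events and reactions.** It defines adverse events as "any unfavorable or unintended signs, symptoms, or diseases that occur during or after the intervention, regardless of whether they are related to the intervention". It notes that "smokers may experience a range of withdrawal symptoms after quitting or reducing smoking" and continues: "These symptoms include smoking cravings, anxiety, depression, restlessness, headache, increased salivary gland secretion, lack of concentration, and sleep disorders". Under Management System it says: "In light of the potential adverse reactions mentioned above, the researchers will conduct daily inquiries during the intervention". For any adverse reaction it provides an assessment, takes account of what the person wishes, and ends as follows: "a collective decision will be made by the medical school, psychology department, and participant regarding their continued participation in the subsequent research".

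Three other places bear on the point. Outcome Measures repeats the daily questioning and groups withdrawal symptoms with adverse reactions: "Researchers will inquire daily during the intervention period whether participants experience tobacco withdrawal symptoms or any other adverse reactions". Sample size estimation takes smoking urges on the QSU-Brief as the primary outcome, and Outcome Measures lists subjective craving among the primary outcomes. Item (2), Participant Exclusion, treats fewer than 5 sessions as an incomplete intervention and offers two responses, exclusion or adjustment by a mixed model.

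**The concern.** A stopping rule for safety normally separates what is serious from what is expected. Item (5) does not, and the broad definition of an adverse event does nothing to narrow it. Craving is both a listed withdrawal symptom and the construct that the trial is meant to change. It is asked about every day of training.

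A report of craving is foreseeable in someone who cuts down. Research background cites earlier work in which brief mindfulness training lowered cigarette consumption. The adverse-event section says that withdrawal starts within hours and peaks within 14 days, so the one-week course falls inside that window for anyone who cuts down at its start. The closing section on participants after the trial says that the training teaches people to notice and accept craving when it comes. Under item (5), reporting that craving can end the training.

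At stake are who receives the full course, whether two staff members would treat the same report alike, and possibly who is analysed.

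**Working it through.** The point rests on the text. The plan states no figure for it, so there is none to reproduce.

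**Step 1: do both rules cover the same symptom?** Item (5) speaks of adverse events, while the joint decision applies to adverse reactions. The difference does not separate them. Item (5) names withdrawal symptoms expressly, and the Management System text calls the listed symptoms potential adverse reactions. Outcome Measures pairs them in the same way. A craving report after cutting down therefore falls under both.

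**Step 2: what does each rule do?** Item (5): discussion, then the intervention ends. Adverse-event section: assessment, then a joint decision on continued participation. No sentence says which comes first or whether one limits the other.

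**Step 3: what follows from a stop?** Item (5) is silent on the data. If training stops before the fifth session, item (2) applies on its face and allows exclusion or model adjustment. Item (2) is framed around the intervention group's training.

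**Step 4: how many people might be affected?** The documents give no report rate, so the daily rate p is an assumption. Assume also one session and one inquiry per day, with every report leading to a stop. The share stopped before session 5 is:

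- p, if the same people report every day;
- 1 − (1 − p)^4, if days are independent and the inquiry follows the session;
- 1 − (1 − p)^5, if days are independent and the inquiry precedes the session.

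| Assumed p | Same people daily | Independent, after session | Independent, before session | Of 45, lowest to highest |
|---|---|---|---|---|
| 2% | 2% | 7.8% | 9.6% | 0.9 to 4.3 |
| 5% | 5% | 18.5% | 22.6% | 2.2 to 10.2 |
| 10% | 10% | 34.4% | 41.0% | 4.5 to 18.4 |
| 20% | 20% | 59.0% | 67.2% | 9.0 to 30.3 |

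Sample size estimation plans 45 in the experimental group for 34 needed, an allowance of (45 − 34)/45 = 24.4%. If everyone stopped were also excluded, and days were independent, the allowance would be used up at p = 1 − (1 − 0.244)^(1/4) = 6.8% or p = 1 − (1 − 0.244)^(1/5) = 5.5%. The protocol fixes neither condition.

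**The case against.** There is a serious case on the other side, and much of it stands.

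- **A reader might infer that the two sections contradict each other.** The documents do not go that far. Item (5) ends the intervention, while the joint decision concerns participation in the later research. Read in sequence, training stops and the parties then decide about what remains. The protocol does not state this sequence, but the wording allows it. What remains is a missing link between the rules, and the sequential reading leaves the missing severity threshold untouched.
- **A reader might infer that participants are removed on their primary outcome.** They are not. The trigger is a symptom reported at a safety inquiry, not a score on the QSU-Brief or another craving scale. The protocol ties withdrawal to quitting or reducing, and it asks only for 3 hours without smoking before visits. Ordinary craving in someone still smoking as usual need not count. The overlap is with the construct.
- **A reader might infer that stopped participants leave the analysis.** Item (5) does not say so, whereas the items on withdrawal and suspension do say when people or data are left out. Item (2) is hedged and offers adjustment as an alternative. Exclusion is a possible consequence only.
- **The background work shows craving falling along with consumption.** It therefore does not predict more craving reports. It supports only that cutting down is foreseeable.
- **A low threshold is a cautious safety choice**, and the trial has no separate safety committee. That is fair, but a medical assessment before stopping also protects participants, and the protocol already provides one.
- **The assumed rates carry little evidence.** A range of about 1 to 30 of 45 excludes almost nothing.

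**Conclusion.** The point holds in a limited form. Item (5) is a stated rule that, taken literally, ends training for mild and expected symptoms. Its relation to the joint-decision rule is left open. Exposure to training can then depend on a symptom that overlaps the primary outcome construct, and a stop before session 5 can lead to exclusion or adjustment.

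The conclusion assumes that staff apply item (5) as written and that some participants cut down and report symptoms during the week. Neither the size nor the direction of any bias can be derived from the documents. The rates in the table are illustrative and should not be used to grade the point. It is worth correcting because the rule is avoidable and the change is small.

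**What to change.** Make three edits.

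1. **Item (5).** State that an adverse event triggers the assessment in the adverse-event section, and that the medical school, the psychology department and the participant then decide jointly whether training stops. State that expected craving or mild withdrawal symptoms are recorded and do not by themselves end training.
2. **Item (2).** Add one line: anyone whose training is stopped for an adverse event stays, with consent, in scheduled follow-up and in the between-group analysis as randomised. The exclusion for fewer than 5 sessions does not apply to them.
3. **Adverse-event section.** Add a cross-reference to item (5), so that one rule covers both training and later participation.

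The cost is a few sentences. Study design says that the trial has not started, and no new staff or visits are needed. The downside is that the stop becomes less automatic, so the ethics committee should see the change.

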1. ***Inclusion and exclusion criteria. [Inclusion criteria define the main body of the study and determine the representativeness of the study population; exclusion criteria define individuals within the study population that may affect the study and determine the homogeneity of the study population]***

Inclusion criteria (1) Right-handed. (2) Smoking an average of 10 or more cigarettes per day (half a pack of cigarettes). (3) Smoking history of at least 1 year. (4) Exhaled carbon monoxide (CO) levels detected by instruments are between 10-7ppm or lower (abstinent from smoking cigarette for 3 h prior to every visit). (5) Age between 18 and 40 years old. (6) Normal vision or corrected to normal vision. (7) Normal mental and physical health conditions (PHQ-9 **^[22-24]^** total score <20, GAD-7 **^[25, 26]^** total score <11). (8) Meet the diagnostic criteria for tobacco use disorder in DSM-5 (through clinical semi-structured interviews **^[27]^**).

Exclusion criteria: (1) Asthma, contact dermatitis, or allergies to silicone. (2) Recent use of corticosteroid medications within the past 3 months. (3) Practiced any meditation, yoga, tai chi, or qigong for more than 20 hours in the past year or lifetime, participated in meditation or yoga retreats, and attended any meditation courses. (4) Not suitable for EEG (e.g., metal implants, severe head trauma and electrode allergy). (5) PHQ-9 total score ≥20. (6) GAD-7 total score ≥11. (7) Adhere to specific religious beliefs and therefore unable to participate in meditation as required by the program. (8) Currently participating in similar trials or other neurophysiological experiments.

1. ***Study design, design pattern diagram, with SPIRIT template attached. [Clearly state the design scheme used in this study, such as: consecutive case or single-arm design, cross-sectional study, case-control study, cohort study, including historical cohort study or prospective cohort study, nested case-control study, randomized controlled trial, clearly specify the type, such as parallel design, crossover design, factorial design, single-group design; for treatment studies, specify the type of research objective framework, such as superiority, equivalence, non-inferiority, exploratory]***

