**Fig 3. Study Design and Procedure**

*The upper portion of the figure illustrates the overall study design. The middle portion depicts the timeline for assessing scales and EEG at baseline, post-intervention, and follow-up timepoints. Brief mindfulness and relaxation training will be administered to both the intervention and control groups after recruitment. The baseline assessment (-T1, T0) will be completed before the intervention. Audio guidance will be provided for daily practice in the BMT group, while there will be no additional practice or intervention for the control group after training. The lower portion of the figure represents the modules of psychological and behavioural assessments during the baseline and five follow-up sessions. The cue-reactivity task will be implemented using a customized two-choice oddball paradigm. INT: intervention, rs-EEG: resting-state EEG; BMT: brief mindfulness training; VAS: Visual analogue scale; SMT: state-mindfulness.*

1. ***Sample size estimation. [List the four elements: δ(Δ) or π1, π2, α, β or Power, and provide the calculation formula]***

In this study, the subjective reports of smoking urges (QSU-Brief) will be used as the primary outcome measure. Referring to study of similar populations **^[28]^**, We set δ(Δ)_tot_ = 4 to represent the anticipated reduction of 4 points in the QSU-Brief score after the intervention in the experimental group. Multiple measurements of the QSU-Brief will be conducted on participants before and after the training, as well as during the 60-minute online training period. To estimate Cohens’d, we have set α = 0.05 and β = 0.80. Cohens’d can be calculated using the formula Cohens’d=(δ(Δ)/SD_estimate_), where the estimated SD_estimate_ was 7.65 based on reference study. Therefore, the corresponding command is pwr.t.test (d=cohens_d, sig.level = 0.05, power = 0.80, type = "paired", alternative = "two.sided"), and the estimated sample size is 34. Therefore, the minimum required sample size for the experimental group is 34. Considering a natural dropout rate of 30%, the sample size for the experimental group should be no less than 45.

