| **Affect** | -T1, T0, T1-T5 | **Positive And Negative Affect Scale（PANAS）**compiled by Watson et al. **^[39]^**, Chinese version **^[40]^** includes 10 corresponding adjectives that described either positive or negative emotion in both the both the negative and positive affect scales. Each project scores 1-5 points, with a total score of 10-50 points. to measure the emotional feelings of the past week. | secondary |
| **VAS for affect** | -T1, T0, T1-T5, during CR task | **Visual analogue scale (VAS)** for affect administered during cue-reactivity experiment to measure the state of affect, including valence and arousal. | secondary |
| **Impulsiveness** | -T1, T0, T1-T5 | **The Barratt Impulsiveness Scale Version 11 (BIS-11)** **^[41]^** was revised in 1995, consisting of a total of 30 items. The revised Chinese version **^[42]^** consists of 30 items, including three dimensions: motor impulsiveness, cognitive impulsiveness, and no planning impulsiveness, with a total score of 30-150, High scores represent hyperactivity, lack of concentration, and lack of planning, respectively. The higher the factor scores of each subscale, the stronger the impulsivity. | secondary |
| **Record of daily practice for mindfulness** | T0, T1 | Self-report of practice time; cognitive, emotional and behavioural states; course feedback and suggestions. | others |
| **Adverse events** | T0, T1-T5 | Proactive reporting without time constraints during research period. | others |
| **Socio-demographic** | -T1 | Age, gender, major, education year, Handedness | others |
| **Handedness** | -T1 | **Edingburgh Handedness Inventory（EHI）**is a measurement scale used to assess the dominance of a person’s right or left hand in everyday activities, sometimes referred to as laterality **^[43]^**, the Chinese version will be used**^[44]^**. | others |
| **Depression** | -T1 | **Patient Health Questionnaire (PHQ-9)** **^[23]^** self-administered tools for assessing depression for recent two weeks, with each project scoring 0-3 points and a total score of 0-27 points, with 6-9 points, 10-14 points, 15-21 points and 22-27 points indicating mild, moderate, severe and extreme severe depression. | others |

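### The daily withdrawal-symptom inquiry has no like-for-like reading before training, so symptoms already present can be logged as adverse events and dilute any account of harms by arm

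*Protocol*

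**What the plan says.** Two sections of the protocol place the prompted inquiry in the training week. Outcome Measures states: "Researchers will inquire daily during the intervention period whether participants experience tobacco withdrawal symptoms or any other adverse reactions". The Management System paragraph of the adverse-event section repeats it: "the researchers will conduct daily inquiries during the intervention to determine whether participants have experienced any of the symptom". The symptoms meant are those given at the start of that section: "These symptoms include smoking cravings, anxiety, depression, restlessness, headache, increased salivary gland secretion, lack of concentration, and sleep disorders".

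The same section defines an adverse event as "any unfavorable or unintended signs, symptoms, or diseases that occur during or after the intervention, regardless of whether they are related to the intervention". It has no rule for a symptom that was there before training or that has become worse.

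Table 1 lists adverse events at T0 and T1-T5, at outcome level others, with this method: "Proactive reporting without time constraints during research period". T0 precedes training, as the Fig 3 legend says: "The baseline assessment (-T1, T0) will be completed before the intervention".

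Those enrolled have tobacco use disorder and smoke at least 10 cigarettes a day. The exclusion limits for mood and anxiety are "5) PHQ-9 total score ≥20. (6) GAD-7 total score ≥11", so PHQ-9 up to 19 and GAD-7 up to 10 may enter.

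Item (5) of the section on participant effectiveness determination adds that "any adverse events (including tobacco withdrawal symptoms) will be considered termination criteria".

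**The concern.** Several of the listed symptoms are ones that a current smoker may well have on an ordinary day. Craving is also what the trial sets out to reduce. A yes on day 1 of training therefore does not show whether the symptom began with training, worsened with it, or was simply the participant's usual state.

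Two things are at stake. The first is how harms under mindfulness training and relaxation can be described: a shared background of old symptoms raises both arms' counts and narrows the gap between them. The second is the judgement on causality. The protocol defines adverse reactions as causally related to the intervention, and whether onset came before or after training is basic to that judgement. A T0 reading that was never taken cannot be supplied by a later analysis plan.

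**Working it through.** **Text check: what is known about each listed symptom before training**

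- Craving: TCQ-SF, QSU-Brief and a VAS at -T1 and T0, repeated at T1-T5.
- Depression and anxiety: PHQ-9 and GAD-7 at -T1 only, with a two-week recall. PANAS and the affect VAS at -T1 and T0, repeated at T1-T5, cover affect in general.
- Poor concentration: touched by BIS-11 at -T1 and T0, repeated at T1-T5, as a facet of impulsiveness.
- Restlessness: no scale is named for it as such.
- Headache, salivation and sleep: no repeated scale is named.
- The list itself: not asked. The T0 adverse-event entry is by participant-initiated report, and under the definition nothing before training is yet an adverse event.

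The overlap is partial, in other formats and recall periods, and no rule ties any of these scales to the daily inquiry.

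**Illustration of size**

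The protocol gives no adverse-event rate, symptom prevalence or power for harms, so there is no stated figure to reproduce.

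Inputs:
- n = 45 per arm. Sample size estimation gives 45 as the minimum for the experimental group. The control size is not stated there and is assumed equal.
- New-onset risk over the training week: 10% v 30% (assumed).
- Background b, the share who already have a listed symptom, equal in both arms: 30%, 60% or 90% (assumed).

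Formulas:
- Recorded risk without a baseline reading = b + (1 − b) × p, where p is the new-onset risk. The difference between arms becomes (1 − b) × 20 points.
- With a baseline reading, counting new onset only, the comparison uses the n × (1 − b) per arm who are symptom-free at T0, and the difference stays at 20 points.
- Power, two-sided 5%, normal approximation = Φ[(d − 1.96 × se0) / se1], where d is the difference, se0 = √(2 × p̄(1 − p̄)/n), p̄ is the mean of the two risks, and se1 = √((p1(1 − p1) + p2(1 − p2))/n).

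Worked for b = 60%:
- Without baseline: 0.60 + 0.40 × 0.10 = 0.64 and 0.60 + 0.40 × 0.30 = 0.72, so d = 0.08. se0 = √(2 × 0.68 × 0.32/45) = 0.0983 and se1 = √((0.2304 + 0.2016)/45) = 0.0980. Power = Φ[(0.08 − 0.1927)/0.0980] = Φ(−1.15) = 12.5%.
- With baseline: n = 45 × 0.40 = 18, risks 0.10 and 0.30. se0 = √(2 × 0.20 × 0.80/18) = 0.1333 and se1 = √((0.09 + 0.21)/18) = 0.1291. Power = Φ[(0.20 − 0.2613)/0.1291] = Φ(−0.475) = 31.7%.

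| Background b | Recorded risks, no baseline | Difference | Power, no baseline | n per arm free at T0 | Power, new onset only |
| --- | --- | --- | --- | --- | --- |
| 0% | 10% v 30% | 20 points | 66.5% | 45 | 66.5% |
| 30% | 37% v 51% | 14 points | 26.5% | 31.5 | 51.0% |
| 60% | 64% v 72% | 8 points | 12.5% | 18 | 31.7% |
| 90% | 91% v 93% | 2 points | 5.4% | 4.5 | 10.6% |

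The last row shows direction only, since a normal approximation is not reliable with 4.5 per arm. Counting worsened symptoms as well could add power. That is not modelled.

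**The case against.** A reader might infer that the harm comparison between arms is swamped, with event rates near saturation and a real excess invisible. The documents do not support that. They plan no between-arm test of harms, they rank adverse events as others, and they give no prevalence from which saturation could be shown. The design points to common background symptoms, craving above all, but how common is an assumption.

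Nor would a baseline reading bring power back to about 66%. That figure belongs to a group with no background symptoms at all. Once some participants already have the symptom, fewer can show a new onset, and the comparison stays weak with or without the checklist.

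Randomisation also helps. Background should be similar in the two arms, so it dilutes the contrast rather than producing a false one, and the control arm is itself a reference. The move from unprompted reports at T0 to prompted ones in training would distort a before-after comparison of adverse events, but it affects both arms and no such comparison is planned. Medical and psychology staff are to assess anyone with an adverse reaction, which may clarify individual cases. Finally, a symptom that occurs during the intervention can be read as one that starts then.

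All of this limits the consequence. It does not remove the gap. On either reading of the definition, the prompted data alone cannot show onset. The staff assessment comes after the report and has no earlier answer on the same list to consult. A statistical analysis plan could set a rule for new or worsened symptoms, but it would have no matching T0 reading to apply it to.

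**Conclusion.** The point holds in a limited form. The prompted inquiry has no like-for-like pre-training reading, and the adverse-event definition does not distinguish old symptoms from new or worsened ones, so pre-existing symptoms can be logged as adverse events. The effect is to dilute any description of harms by arm: a true difference shrinks by the factor 1 − b. On the assumed figures above, at 60% background a 20-point difference is recorded as 8 points. A T0 reading restores the 20 points but raises power only from 12.5% to 31.7%. These sizes rest on assumed background and onset rates, equal background in the two arms, and an assumed control arm of 45.

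There is also a contradiction on participant management. Item (5) on participant termination makes any adverse event, withdrawal symptoms included, a termination criterion. The Management System paragraph instead leaves continued participation after an adverse reaction to a joint decision with the participant. As written, a symptom that predates training could meet the first of these. The two passages must be reconciled. Which of them should prevail is not a question for this review.

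**What to change.** Before enrolment starts, add one reading at T0: the identical symptom list, with the same prompting and a simple severity grade, asked of all participants before allocation. The protocol already allocates groups only after baseline data are complete, so no extra visit is needed.

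State that, for analysis and reporting only, symptoms that are new or worse than at T0 are summarised by arm, next to all raw reports. Leave the adverse-event definition used for participant management as it stands. Because it feeds the termination criterion, rewriting it for counting purposes could change who meets that criterion.

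Separately, reconcile the termination item with the Management System paragraph.

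The cost is a few minutes per participant at T0 and a sentence or two of text. Headline counts of new or worsened symptoms will be lower than the raw daily answers, which is why both should be shown.
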